**For Type 2 diabetes:**

1. Initial hourly basal insulin rate will be estimated as  $(BW \times 0.4)/24$  units of insulin
2. The initial carbohydrate to insulin ratio for meal boluses will be estimated as  $450/(BW \times 0.84)$  (grams of carbohydrate per unit insulin)
3. Initial correction factor for fasting glycemia  $>110$  mg/dL, postprandial  $>140$  mg/dL will be estimated as  $1700/(BW \times 0.8)$  for capillary glucose drop per unit insulin

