**For Type 1 diabetes:**

1. Initial hourly basal rates will be estimated as  $(BW \times 0.2)/24$  units of insulin
2. Initial meal boluses using a carbohydrate to insulin ratio will be estimated as  $450/(BW \times 0.2)$  (grams of carbohydrate per unit insulin)
3. Initial correction factor for fasting glucose  $>110$  mg/dL, postprandial  $>140$  mg/dL will be estimated as  $1400/(BW \times 0.4)$  for capillary glucose drop per unit insulin

Alternatively, for those patients who are using a Basal-Bolus approach to control their Type 1 diabetes, the insulin pump may be programmed to use their current basal dose and carbohydrate to insulin ratios as well as correction factor.

**For those patients who are already on insulin pumps,** the insulin parameters will be adjusted based on the best prediction of needs using results from both finger stick data and baseline (run-in period) RT-CGM data.

Overall the targets for glycemia management will be:

1. Fasting glucose: 80-120 mg/dL
2. Postprandial excursions: 100-180 mg/dL

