patients will drink a cup (150 mL) of refrigerated (at 4 degrees C) Ensure® (1.1 kcal/mL) at a rate of 150 mL every 5 minutes until they feel completely full. Patients will drink from an opaque cup which will be filled out of sight so that the volume consumed is not readily apparent to minimize the potential of introducing an assessment bias. In addition, no information regarding the total volume of Ensure® ingested will be communicated to the patient. The total volume of Ensure® ingested will be recorded on the EGG and Satiety Test form. The satiety test will be analyzed by the total amount of Ensure® consumed. Symptoms of nausea, bloating, abdominal discomfort, hunger, and stomach fullness will be recorded on a visual analog scale at baseline and at 10, 20, 30, and 60 minutes after ingestion of Ensure®. The electrodes will then be removed. The EGG will be analyzed for the fasting and post nutrient load periods corresponding to symptom assessments at 0-10, 11-20, 21-30, 31-40, 41-50 and 51-60 minute intervals. The percentage distribution of the power in the normal frequency range (2.5-3.75 cycles per minute [cpm]), tachygastria (>3.75-10 cpm), bradygastria (<2.5 cpm) and duodenal-respiration (>10 cpm) will be calculated. A power ratio comparing mean signal amplitudes between postprandial and preprandial power will be calculated. The dominant frequency, and the percentage of time in the dominant frequency will be calculated and recorded.

Patients will receive 1 unit of insulin for every 15 grams of Ensure® consumed during the caloric satiety testing to reduce the likelihood of severe postprandial hyperglycemia. Patients blood glucose levels will be closely monitored using their home glucose meter. Patients will be monitored for 2 hours after beginning the Ensure® satiety testing to assure their blood glucose level does not exceed 300 mg/dL. If a patient's blood glucose level exceeds 300 mg/dL, additional insulin will be given to bring it down to 250 mg/dL as per the suggestion of the endocrinologist or diabetes educator of the team.

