EGG will be analyzed for the fasting and post nutrient load periods corresponding to symptom assessments at 0-10, 11-20, 21-30, 31-40, 41-50 and 51-60 minute intervals. The percentage distribution of the power in the normal frequency range (2.5-3.75 cycles per minute [cpm]), tachygastria (>3.75-10.0 cpm), bradygastria (<2.5 cpm) and duodenal-respiration (>10 cpm) will be calculated. A power ratio comparing mean signal amplitudes between postprandial and preprandial power will be calculated. The dominant frequency and the percentage of time in the dominant frequency will be calculated and recorded.

Patients will receive 1 unit of insulin for every 15 grams of Ensure® consumed during the caloric satiety testing to reduce the likelihood of severe postprandial hyperglycemia. Patients' blood glucose levels will be closely monitored using SMBG supplemented with the RT-CGM. Patients will be monitored for 2 hours after beginning the Ensure® satiety testing to assure their blood glucose level does not exceed 300 mg/dL. If a patient's blood glucose level exceeds 300 mg/dL, additional insulin will be given to bring it down to 250 mg/dL as per the suggestion of the endocrinologist or the diabetes educator.

**Autonomic function with ECG:** Patients will have a follow-up ECG done followed by an ECG tracing for heart rate variability. Patients will be requested to remain in the supine position while breathing slowly for a five minute period. From this ECG tracing, vagal cholinergic function will be estimated by quantifying changes in heart rate during inspiration and respiration. R-R interval will be analyzed for mid and high frequency fluctuations (max to min ratio normal is 30:150).

**Week 16 visit:** Patients will meet with a diabetes educator to review blood glucose levels and to make necessary adjustments to insulin doses by changing parameters of the insulin pump. The Follow-up Medical History form will be completed. Any unanticipated adverse events will be reviewed with the patient and recorded on case report forms.

**Week 20 visit:** Patients will meet with a diabetes educator to review blood glucose levels and to make necessary adjustments to insulin doses by changing parameters of the insulin pump. The Follow-up Medical History form will be completed. Any unanticipated adverse events will be reviewed with the patient and recorded on case report forms.

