#### Meal Boluses

The adjustment for meal related glycemia is of special interest in the GLUMIT-DG study since gastric emptying may be erratic and delayed. For the GLUMIT-DG study, the following guidelines will be used for adjustment of meal boluses at all subsequent follow-up visits or phone contacts.

Insulin administered for meal(s) will be tailored using a dual wave pattern. The amount of insulin for the specific meal will be estimated using the carbohydrate to insulin ratio (CHO:I). This ratio is the estimated amount of meal carbohydrate that one unit of insulin metabolizes. This ratio is calculated initially by the following formulas (see also Section 3.3):

(1)  $450/(\text{BW (kg)} \times 0.84)$  for Type 2 diabetes, and

(2)  $450/(\text{BW (kg)})$  for Type 1 diabetes

The carbohydrate to insulin ratio is in the following units: grams of meal carbohydrate for every unit of insulin. The ratio is entered into the insulin pump. When the patient is about to eat or has already eaten, he/she enters into the pump the estimated amount of carbohydrate ingested during the meal or the meal the patient is preparing to eat. The microchip in the pump uses the pre-entered CHO:I ratio to calculate the bolus of insulin to be delivered. For example, if the meal carbohydrate is calculated as 90 grams and the CHO:I ratio is 30, then the pump will calculate a total of 3 units of insulin. If the same amount of meal carbohydrate is eaten and the CHO:I ratio is 10, then the total amount of meal insulin calculated is 9 units. Thus a higher CHO:I ratio yields a lower calculated insulin bolus and vice versa. The pump will prompt the user to confirm acceptance of the suggested dose and will not deliver the bolus unless the patient accepts the suggestion from the pump.

The bolus of insulin can be delivered in TOTAL during a short period of time (standard bolus) or it can be

delivered over a prolonged period of time (extended or square wave bolus). A dual wave bolus can be configured by delivering a certain % of the dose immediately (standard bolus) and the rest over several hours after meal ingestion (extended square wave bolus). These times can be tailored as per the judgment of the diabetologist and diabetes educator. For obvious reasons, the second approach is better suited for patients with gastroparesis since it diminishes the possibility of hypoglycemia and will be used in the GLUMIT-DG study.

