| 181-250                     | >250                        | Decrease by 2                           | Decrease by 10%                                                                 | 11         |
| >250                        | <80                         |                                         | Increase by 20%                                                                 | 12         |
| >250                        | 80-180                      |                                         | Increase by 10%                                                                 | 13         |
| >250                        | 181-250                     | Decrease by 1                           | Increase by 10%                                                                 | 14         |
| >250                        | >250                        | Decrease by 2                           |                                                                                 | 15         |

\* CHO:I ratio = grams of carbohydrate in the meal: per one unit of insulin (this ratio estimates the amount of carbohydrate in grams that are metabolized by 1 unit of insulin)

\*\* The % bolus is the amount of meal insulin delivered in the first hour after initiation of bolus administration; extended is the amount of insulin delivered in the subsequent 2-4 hours.

Columns 1 and 2 in the table indicate the glycemia at time = 1 hour (column 1) and time = 3 hours (column 2) AFTER meal ingestion. Column 3 indicates the suggested change in carbohydrate:insulin ratio (CHO:I). As can be seen from the Table, when glucose values are low, then the CHO:I ratio is suggested to be increased (see row #1 as specific example) to decrease the total amount of meal insulin delivered in subsequent meals. Contrary to the latter, the CHO:I needs to be decreased if the glucose is high (see last row for specific example). Since the process is cumulative, if the glucose levels are not corrected with an initial change in the CHO:I ratio, then it can be adjusted again when new glucose levels are available.

The distribution of the insulin bolus (as a percent distribution for the post meal period) will also be adjusted based on the finger stick at hour = 1 and hour = 3. The actual change in percentage itself will

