#### Mild hypoglycemic episodes

For a **hypoglycemic event** to be considered mild; the capillary glucose will be 50 - 70 mg/dL as confirmed by a finger stick glucose meter reading (SMBG); and the patient is fully capable of self treatment without the need of third party assistance. Mild hypoglycemia may be symptomatic or asymptomatic. The following treatment protocol for mild hypoglycemic episodes will be followed:

1. If the SMBG value is 50 - 70 mg/dL, it should be treated by ingestion of 15-20 grams of carbohydrates (e.g., 4-5 glucose tablets, 5-6 Lifesavers, 4-6 oz. of a regular [non diet] soft drink, or 8 oz. low fat milk, or 4 teaspoons of sugar dissolved in a liquid or juice). If the subject is in the hospital, the SMBG reading will be confirmed by a laboratory glucose measurement, but treatment will be initiated based on the Ultra reading.
2. Blood glucose should be self-tested 15-20 minutes after ingestion of carbohydrates and therapy will be repeated as above, as needed. Cycle should be repeated until glucose level is 80 mg/dL or above.
3. Once episode is resolved, if no meal is scheduled the next 2 hours, a mixed nutrient snack, including a carbohydrate, protein, and fat will be ingested right after the initial therapy and after resolution of episode to prevent another episode.

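### Satiety-test insulin is ordered per 15 grams of Ensure rather than per 15 grams of carbohydrate, which read literally is at least about 3.4 times the dose at 1:15 on carbohydrate

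*Protocol*

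**What the plan says.** Section 5.3, on caloric satiety testing at screening, orders: "Patients will receive 1 unit of insulin for every 15 grams of Ensure® consumed during the caloric satiety testing". The week 12 and week 24 descriptions in Section 5.6 carry the same rule ("Patients will receive 1 unit of insulin for every 15 grams of", followed by the product name). The drink is given in 150 mL cups at 1.1 kcal/mL, "at a rate of 150 mL every 5 minutes until they feel completely full", and the quantity recorded is a volume.

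Elsewhere the protocol doses meal insulin on carbohydrate:

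- Section 3.3, type 2: "The initial carbohydrate to insulin ratio for meal boluses will be estimated as" 450/(BW × 0.84).
- Section 3.3, type 1: "Initial meal boluses using a carbohydrate to insulin ratio will be estimated as" 450/(BW × 0.2).
- Section 5.7, Meal Boluses, gives the unit of the ratio as "grams of meal carbohydrate for every unit of insulin".
- The footnote to the titration table in Section 5.7 defines it again as "grams of carbohydrate in the meal: per one unit of insulin".

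The hypoglycemia rules in Section 6.2 keep the same distinction. For a mild episode, "it should be treated by ingestion of 15-20 grams of carbohydrates", with product amounts such as tablets or ounces of drink listed separately as examples.

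**The concern.** The satiety-test order departs from the protocol's own convention at a point where the unit decides an insulin dose. A liquid feed is mostly not carbohydrate by weight, so grams of product and grams of carbohydrate give very different doses.

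The patients are fasting and were selected for delayed gastric emptying. Section 5.4 itself warns of a mismatch between the bolus and nutrient absorption in this population. Screening is the most exposed visit. Section 4.2 admits patients on oral agents only, and Section 5.3 tells insulin users to withhold their own meal insulin, so this order is the meal-dose rule in force. Patients are also not told how much they drank, so they cannot check the dose themselves.

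Meter readings below 70 mg/dL also feed the primary safety outcome (Section 8.2). A low caused by a test dose could therefore be counted there, although I put no size on that.

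**Working it through.** The protocol states a rule but no resulting dose, so there is no figure of its own to reproduce. The check compares the dose under the two readings of the gram.

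**Inputs from the protocol.** Cup volume 150 mL; energy density 1.1 kcal/mL; 1 unit per 15 g; starting ratio formulas in Sections 3.3 and 5.7.

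**Assumptions, not in the protocol.** Density of the product 1.0 to 1.1 g/mL; 3.75 to 4 kcal per gram of carbohydrate. All energy is treated as carbohydrate, which gives an upper bound. Any fat or protein in the product lowers the carbohydrate and widens the gap.

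**Literal reading, per cup.** 150 mL × 1.0 to 1.1 g/mL = 150 to 165 g; divided by 15 = 10 to 11 units.

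**Carbohydrate reading, per cup.** 150 × 1.1 = 165 kcal. 165/4 = 41.25 g and 165/3.75 = 44 g. Divided by 15, the dose is at most 2.75 to 2.93 units.

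**Comparison.**

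- Ratio: 10/2.93 = 3.4 up to 11/2.75 = 4.0.
- Gap per cup: 10 − 2.93 = 7.07 up to 11 − 2.75 = 8.25 units.
- Two cups: 20 to 22 units against at most 5.5 to 5.9.

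**Against the protocol's individual starting ratios.** The table takes a 70 kg patient, one cup, the literal dose at its lower value of 10 units, and 41.25 to 44 g of carbohydrate.

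| Formula | g per unit | Units for one cup | Literal dose as a multiple |
|---|---|---|---|
| Type 2: 450/(70 × 0.84) | 7.65 | 5.39 to 5.75 | 1.74 to 1.86 |
| Type 1, Section 5.7: 450/70 | 6.43 | 6.42 to 6.84 | 1.46 to 1.56 |
| Type 1, Section 3.3: 450/(70 × 0.2) | 32.1 | 1.28 to 1.37 | 7.3 to 7.8 |

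The two type 1 formulas differ by a factor of five. That is a separate inconsistency, so the last row is unsettled and the conclusion does not rest on it.

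**Weight at which the excess over the ceiling disappears** (literal dose 10 units).

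- Type 2: 4500/(44 × 0.84) = 121.8 kg to 4500/(41.25 × 0.84) = 129.9 kg.
- Type 1, Section 5.7: 4500/44 = 102.3 kg to 4500/41.25 = 109.1 kg.

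**The case against.** The strongest reply is that nobody would follow the literal reading. Ensure is poured and recorded by volume, and the protocol gives neither a density nor an instruction to weigh it, so a dose per gram of product cannot be worked out from the text alone. In the other insulin and glucose-treatment rules, grams are grams of carbohydrate or sugar. Section 6.4 calls the satiety-test insulin a meal bolus, and Section 5.7 doses meal boluses on carbohydrate. From run-in visit 3, patients are told to give meal insulin only through the pump's bolus wizard, which takes carbohydrate. On this view a word is missing and no calculation is wrong.

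There are also real safeguards:

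- consultation with the endocrinologist 24 hours beforehand;
- a pre-test glucose of 100 to 270 mg/dL;
- close meter monitoring for two hours;
- the treatment rules for low glucose in Section 6.2;
- at weeks 12 and 24, the RT-CGM low alarm at 80 mg/dL and a bolus that starts only once glucose is rising.

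The standard operating procedures and the satiety test form are not shown and may carry a carbohydrate figure. Finally, the 3.4-fold contrast is with 1:15 on carbohydrate, a presumed intent. Against the weight-based ratios the excess is smaller and vanishes in heavy patients.

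Most of this stands as far as likelihood goes: trained staff would probably notice. It does not make the order right. The bolus-wizard and RT-CGM safeguards are not generally available at screening, where the study pump has not been issued and the iPro displays no readings. Section 6.4 changes when the bolus starts, not its unit. The stated purpose of the two-hour watch is to prevent glucose above 300 mg/dL, and the low-glucose rules act only after a low has occurred. Safety then depends on staff departing from the written instruction.

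**Conclusion.** The concern holds. As written, the satiety-test order uses the wrong unit at all three test occasions, and nothing in the protocol corrects it. Per 150 mL cup the literal dose is 10 to 11 units against a ceiling of 2.75 to 2.93 units at 1:15 on carbohydrate, an excess of at least about 7 units that recurs with each further cup. This rests on the assumed density and energy per gram of carbohydrate, and the conclusion is the same anywhere in those ranges. That 1:15 was meant for carbohydrate is an inference, though a strong one. The size of the excess is firm against that comparator. Against the individual starting ratios it is about 1.5 to 1.9 times at 70 kg (type 2, and type 1 by Section 5.7). The finding concerns the protocol text and does not show that any patient was dosed wrongly. It should be fixed.

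**What to change.** In Section 5.3 and in both the week 12 and week 24 descriptions in Section 5.6, reword the order as 1 unit of insulin for every 15 grams of carbohydrate in the Ensure consumed. Beside it, state the product's grams of carbohydrate per 150 mL cup, so that staff can go from the recorded volume to the dose without guessing. The cost is a wording change in three places and one added figure, with no new procedure. Whether patients on the pump should use their own carbohydrate ratio for this test is a separate clinical choice for the study diabetologists, and this correction need not wait for it.

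### Insulin for the Ensure test is ordered per 15 grams of product, while other meal insulin is set per gram of carbohydrate; read literally, a 150 mL cup calls for 10 to 11 units rather than at most about 2.9

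*Protocol*

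**What the plan says.** The caloric satiety test is done at screening, week 12 and week 24. In section 5.3 the patient drinks Ensure (1.1 kcal/mL) "at a rate of 150 mL every 5 minutes until they feel completely full", with no maximum volume stated. For the record, "The total volume of Ensure® ingested will be recorded on the EGG and Satiety Test form". The insulin order is "Patients will receive 1 unit of insulin for every 15 grams of Ensure® consumed during the caloric satiety testing". Section 5.6 uses the same words at both follow-up tests: "Patients will receive 1 unit of insulin for every 15 grams of Ensure". None of the three places restates the rule in grams of carbohydrate or gives the carbohydrate content of the drink.

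Other meal insulin in the protocol is based on carbohydrate:

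- Section 3.3, type 2: "The initial carbohydrate to insulin ratio for meal boluses will be estimated as" 450/(BW x 0.84).
- Section 3.3, type 1: "Initial meal boluses using a carbohydrate to insulin ratio will be estimated as" 450/(BW x 0.2).
- Section 5.7, Meal Boluses, gives 450/(BW x 0.84) for type 2 and 450/BW for type 1, and defines the unit: "The carbohydrate to insulin ratio is in the following units: grams of meal carbohydrate for every unit of insulin". The footnote to the titration table in the same section repeats that definition.

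Section 5.4 (run-in visit 3) tells patients to dose meals only through the pump's bolus wizard, which section 5.7 describes as working from the carbohydrate the patient enters. Section 6.4 starts the bolus for the Ensure test once RT-CGM shows glucose rising.

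**The concern.** Grams of a liquid feed and grams of carbohydrate in it are different quantities, and the first is much larger. The dosing sentence uses the first; the protocol's own definition of a meal-insulin ratio uses the second. Someone who follows the sentence as written would give a patient with delayed gastric emptying several times the insulin of a 1-per-15-g carbohydrate rule, and the absolute excess grows with every cup. Section 5.4 itself warns of a mismatch between bolus insulin and nutrient absorption in these patients. Hypoglycemia is the primary safety outcome (section 8.2), so this dosing order deserves an exact unit.

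Screening visit 2 is the most exposed. The test belongs to screening, while study pump and RT-CGM training belong to run-in (section 5.4, appendix 11.2). The iPro worn in screening is blinded (section 5.3), and patients on oral agents alone are eligible (section 4.2). For the same reason the RT-CGM trigger in section 6.4 cannot be applied at that visit.

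**Working it through.** **The protocol's method.** Section 5.7 computes dose = grams of carbohydrate / ratio. Its examples reproduce: 90/30 = 3 units and 90/10 = 9 units ("the CHO:I ratio is 10, then the total amount of meal insulin calculated is 9 units"). The Ensure rule comes with no derivation or total dose, so there is no further figure to reproduce.

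**Inputs from the protocol.** 150 mL per cup, 1.1 kcal/mL, 15 g per unit, and the starting-ratio formulas.

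**Assumptions not in the protocol.** Density 1.0 g/mL (range to 1.1); 4 kcal per g of carbohydrate (range down to 3.75); all energy counted as carbohydrate, which gives the highest possible carbohydrate dose and so the smallest excess.

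**Literal dose per cup** = 150 mL x density / 15
- 1.0 g/mL: 150/15 = 10 units
- 1.1 g/mL: 165/15 = 11 units

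**Carbohydrate dose per cup at 1:15**, upper limit; energy = 150 x 1.1 = 165 kcal
- 4 kcal/g: 165/4 = 41.25 g; 41.25/15 = 2.75 units
- 3.75 kcal/g: 165/3.75 = 44 g; 44/15 = 2.93 units

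**Ratio, literal to carbohydrate**

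| Density | 3.75 kcal/g | 4 kcal/g |
|---|---|---|
| 1.0 g/mL | 10/2.93 = 3.4 | 10/2.75 = 3.6 |
| 1.1 g/mL | 11/2.93 = 3.75 | 11/2.75 = 4.0 |

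These are minima. At 1.0 g/mL and 4 kcal/g, if 80% of the energy were carbohydrate the ratio would be 10/2.2 = 4.5; at 60%, 10/1.65 = 6.1. The ratio does not depend on the number of cups, but the excess does: at least 10 - 2.75 = 7.25 units after one cup and 20 - 5.5 = 14.5 after two.

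**Against the protocol's starting ratios**, at an assumed 70 kg, 1.0 g/mL and 4 kcal/g

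| Formula | g per unit | Units for 41.25 g | Minimum excess |
|---|---|---|---|
| Type 1, 5.7: 450/70 | 6.43 | 6.42 | 10/6.42 = 1.6 |
| Type 2, 3.3 and 5.7: 450/(70 x 0.84) | 7.65 | 5.39 | 10/5.39 = 1.9 |
| Type 1, 3.3: 450/(70 x 0.2) | 32.14 | 1.28 | 10/1.28 = 7.8 |

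The two type 1 rows differ because sections 3.3 and 5.7 print different type 1 formulas.

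**Effect of weight under the section 5.7 ratios.** The all-carbohydrate upper limit reaches the literal 10 units where 41.25 x BW/450 = 10, so BW = 109 kg (type 1), and where 41.25 x BW x 0.84/450 = 10, so BW = 130 kg (type 2). The minimum excess therefore shrinks as weight rises and reaches 1 at those weights.

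**The case against.** The best reply is that nobody would dose by product weight. Ensure is recorded by volume, no weighing is described and no density is given, so the literal rule could not be carried out without a figure the protocol does not supply. Trained diabetes staff would probably read the sentence as carbohydrate. At weeks 12 and 24 the bolus wizard works from carbohydrate, and section 6.4 treats the Ensure insulin as a meal bolus. Other text limits harm: an endocrinologist is consulted beforehand, glucose must be at least 100 mg/dL at the start, the meter is watched for two hours, and section 6.2 covers treatment of any low reading during participation.

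Most of this stands. It makes a slip the likeliest explanation and lowers the chance of harm. It does not correct the unit: no other text says that the Ensure rule means carbohydrate, and at follow-up the result is two conflicting instructions. At screening visit 2 the study pump's wizard is not yet available.

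A reader might infer a fixed overdose of 3.6-fold or more at all three visits. The documents do not support that. The wording occurs at all three, but the risk is not equal. The 3.6 depends on an assumed density and energy factor, and on an inferred target of 1 unit per 15 g of carbohydrate that the protocol never states. Against patients' own starting ratios the minimum excess can be far smaller or larger. A reader might also infer that the test has no low-glucose rule because its own paragraph names only the 300 mg/dL limit; section 6.2 already applies.

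**Conclusion.** The concern holds as an error of unit in an operative dosing instruction. Read literally, the rule gives 10 to 11 units per 150 mL cup, against at most 2.75 to 2.93 units at 1 unit per 15 g of carbohydrate: a minimum of 3.4- to 4.0-fold over densities of 1.0 to 1.1 g/mL and 3.75 to 4 kcal/g, and more if the drink contains fat or protein. Measured against the protocol's starting ratios at 70 kg, the minimum runs from 1.6-fold to 7.8-fold according to diabetes type and formula, and under the section 5.7 ratios it falls with increasing weight. That carbohydrate was intended is an inference, though section 5.7 supports it well. Nothing here shows that any patient would in fact be overdosed. The sentence should be corrected because it governs insulin in a hypoglycemia-safety study, chiefly for screening visit 2. The RT-CGM timing gap at that visit is real but secondary.

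**What to change.** - In section 5.3 and at both places in section 5.6, change the rule to *1 unit of insulin per 15 g of carbohydrate in the Ensure consumed*. At weeks 12 and 24 the patient's own carbohydrate-to-insulin ratio could be used instead, which would also remove the conflict with the bolus wizard. The study endocrinologist should confirm the ratio.
- In section 6.4, state that at screening visit 2, where RT-CGM is not yet in use, the bolus starts when finger-stick glucose is seen to rise.

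The cost is a wording change in four places and one or two extra meter readings on the screening test day. Visits, sample size and outcomes are unaffected.
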